**Figure 2. f2:**
[figure not shown]
Workflow for data storage, transfer, and archiving.

**
*Blinding of results*
**

Subject-specific results from the SpHb and CBC tests will be independently collected and technicians analyzing the SpHb will not be informed of the results of the CBC, and vice versa.

### Data quality control

**
*Equipment standardization and calibration*
**

All laboratory measurements will be conducted according to standardized operating procedures (SOPs) internally developed for the parent study. Specifically, research staff and laboratory technicians will follow exactly the Laboratory SOP, Maternal Clinical SOP, Infant Clinical SOP, and the Anthropometry Quality Assurance and Quality Control (QAQC) SOP. These SOPs describe in detail the required equipment (including test kit models) and instructions for equipment calibration and maintenance, biological specimen collection, specimen processing, sample management, and results reporting. Participating laboratories will also perform scheduled quality checks and were required to enroll in the United Kingdom National External Quality Assessment Scheme (UK NEQAS) for hematology. In addition, for the purposes of this substudy protocol, the five-part differential hemoglobin analyzer and Masimo device will be routinely calibrated according to the company's guidelines. Each Masimo device user will receive training from the company, and we will maintain a daily use log as outlined in the SOP.

**
*Corrective action*
**

SpHb: Cases with reference errors (difference between the SpHb and CBC measurements greater than 0.5 g/dL, missing paired CBC reading), user errors (incorrect device setting) and problematic signal quality checks (low signal stability, low performance improvement quality (low perfusion), low SpHb confidence (ambient light interference) - indicated as spot-check monitoring results on the instrument) will be recorded to quantify the percent of cases with failure using lab-designated SOPs.

If there are errors related to CBC, samples should be re-run in case of any errors. If errors persist, lab designated SOPs (such as a daily QC log) will be used to document the errors and appropriate personnel will be notified. Issues related to blood draw (e.g., hemolysis) will be documented for corrective actions, but more blood will not be drawn.

Statistical analysis will be performed using both per-protocol (PP) (excluding outliers and errors) (n<900) and intention-to-treat (ITT) (including outliers and errors) (n=900) analyses. Different from randomized clinical trials where PP and ITT refer to the exclusion or inclusion of data points when participants do not comply to their assigned treatments, here PP and ITT refer to the exclusion or inclusion of data points when the technician didn’t follow the protocol or user’s manual in correctly collecting blood sample or measuring hemoglobin levels, which may lead to outliers or errors.

**
*Missing data*
**

We will examine the percentage and patterns of missingness of the hemoglobin measurements. In cases where missingness is high (e.g., >10%) or cases where missing probabilities are associated with certain factors, multiple imputations (MI) will be carried out. An inclusive imputation model will be employed with all relevant risk factors and hemoglobin measurements from the same patient at different time points. MI results will be compared to the complete case analysis to test the robustness of our conclusions of missing data.

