### Aim and objectives

The primary aim of this study is to evaluate whether total hemoglobin measures using the Masimo SpHb continuous non-invasive monitoring device are accurate as compared to gold standard CBC laboratory tests using peripheral venous blood samples. To achieve this aim, three statistical objectives were identified:

1.To estimate the level of deviation and agreement between SpHb and CBC values longitudinally.2.To calculate the level of agreement between SpHb and CBC values among binary (healthy versus anemic) and ordinal (mild, moderate, severe anemia versus normal) measures longitudinally.3.To describe sociodemographic and clinical factors affecting the difference between SpHb and CBC values.

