### Sample size considerations

**
*Total sample size*
**

The total sample size of 900 per study site will give 90% power for site-specific analyses to detect a systematic shift (defined as mean difference between each pair of SpHb and CBC divided by the standard deviation of all paired differences) of size 0.108 between the mean of SpHb measurements and the mean of CBC measurements. That is, if the SpHb system shifts from the reference CBC measurements by 10.8% of the SD of the mean difference, the probability that we will detect such a systematic shift using one sample t-test with significance level 0.05 is 90%. The total sample size of 900 will also give 80% power to detect a systematic shift of size 0.093*SD between the mean of SpHb measurements and the mean of CBC measurements. The SD can be calculated in the same way as those in the Bland Altman plots. However, 900 is a very conservative estimate of the sample size and would be sufficient to analyze the three sites independently. Based on our pilot data from Kenya and Pakistan, the mean difference between SpHb and CBC is approximately 0.8 times its SD; even a sample size as small as 19 pairs would provide 90% power using one-sample t-test.

In detecting the extreme differences (i.e. large absolute value) between the SpHb and CBC measures on the same sample, the sample size of 900 will give 99.99% probability to detect the top 1% largest values in the distribution of all differences. It will also give 98.90% probability to detect the top 0.5% largest values in the distribution of all differences, and 93.31%, 83.50%, 59.36% probability to detect the top 0.3%, 0.2%, 0.1% largest values in the distribution of all differences, respectively. With three repeated measures from each of the 900 participants, the listed probabilities are conservative estimates of chances in catching extreme values.

**
*Strata sample size*
**

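### Pairs differing by more than 0.5 g/dL are classed as errors, and the per-protocol set excludes errors: read literally, that set is selected on the quantity Objective 1 estimates

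*Protocol article*

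**What the plan says.** All the relevant text is in the protocol article.

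- **Data quality control, Corrective action, SpHb paragraph.** Three kinds of problem are listed together: reference errors, user errors and signal-quality problems. The first kind reads "Cases with reference errors (difference between the SpHb and CBC measurements greater than 0.5 g/dL, missing paired CBC reading". The use stated there is that such cases "will be recorded to quantify the percent of cases with failure using lab-designated SOPs". No exclusion is mentioned at this point.
- **Same section, analysis sets.** "Statistical analysis will be performed using both per-protocol (PP) (excluding outliers and errors) (n<900". The companion set is "intention-to-treat (ITT) (including outliers and errors) (n=900) analyses". Outliers are given no criterion.
- **Same section, next sentence.** PP and ITT are explained as dropping or keeping data points where the technician departed from the protocol or the manual "in correctly collecting blood sample or measuring hemoglobin levels, which may lead to outliers or errors".
- **Aim and objectives.** Objective 1 is "To estimate the level of deviation and agreement between SpHb and CBC values longitudinally".
- **Sample size considerations.** In the pilot data, "the mean difference between SpHb and CBC is approximately 0.8 times its SD". Neither the sign of the shift nor the SD in g/dL is given.

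**The concern.** In a method-comparison study the paired difference is the outcome. It is the input to the Bland-Altman analysis under Objective 1 and the response variable in the Objective 3 models. A difference above 0.5 g/dL may come from a procedural fault, but it may equally be ordinary device error, which the study exists to measure. The size of the difference cannot tell the two apart.

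If errors in the PP definition takes in the reference errors named just before it, every pair left in the PP set agrees within 0.5 g/dL by construction. The PP bias is then pulled towards zero and the PP limits of agreement are capped by the rule rather than estimated from the device. An outlier exclusion based on the result would act in the same direction. The failure percentage would also mix procedural faults with plain disagreement.

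At stake is whether the PP analysis can be interpreted at all, and whether two analysts reading the same section would build the same PP set.

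**Working it through.** **1. The text, side by side.** The SpHb paragraph makes a difference above 0.5 g/dL one kind of error. The definition that follows, "per-protocol (PP) (excluding outliers and errors) (n<900", has no exemption for that kind. The sentence after it makes the technician's departure from procedure the trigger. A pair that differs by 0.9 g/dL with no recorded departure is therefore excluded under the definition and kept under the explanation.

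**2. Inputs.**
- Threshold: 0.5 g/dL (Corrective action), taken as an absolute difference.
- Mean difference: 0.8 SD (Sample size considerations). The results mirror exactly if the shift is negative.
- SD of the differences in g/dL: not in the document. Assumed range 0.25 to 1.5.
- Normal differences: the article makes this assumption itself under Strata sample size.
- 900 pairs per site, one per participant, for the counts.

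**3. The plan's own figures.** The point rests on no power figure, but the article's standardised shifts behave as stated. A two-sided one-sample t-test at 0.05 gives 90.9% power with 19 pairs at 0.8 SD (stated 90%), 89.9% with 900 at 0.108 SD (stated 90%) and 79.6% with 900 at 0.093 SD (stated 80%). So 0.8 is used as mean difference divided by SD.

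**4. Formulas.** Let m = 0.8 × SD, a = (-0.5 - m)/SD and b = (0.5 - m)/SD. Φ and φ are the standard normal distribution and density functions.
- Share kept: Z = Φ(b) - Φ(a)
- Retained mean: m + SD × [φ(a) - φ(b)]/Z
- Retained variance: SD² × {1 + [aφ(a) - bφ(b)]/Z - ([φ(a) - φ(b)]/Z)²}
- Limits of agreement: mean ± 1.96 × SD of the set concerned

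**5. Worked case, SD 1.0.** m = 0.80, a = -1.3, b = -0.3.
- Z = 0.3821 - 0.0968 = 0.2853, so 71.5% are excluded and 257 of 900 remain.
- Retained mean = 0.80 + (0.1714 - 0.3814)/0.2853 = 0.06.
- Retained variance = 1 + (-0.2228 + 0.1144)/0.2853 - 0.7361² = 0.078, so the SD is 0.280.
- All pairs: 0.80 ± 1.96 gives -1.16 to 2.76.
- Retained pairs: 0.064 ± 0.549 gives -0.48 to 0.61.

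**6. Over the assumed range** (shift 0.8 SD; g/dL):

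| SD | Excluded | Kept of 900 | All pairs: bias (limits) | PP, literal reading: bias (limits) |
|---|---|---|---|---|
| 0.25 | 11.8% | 794 | 0.20 (-0.29 to 0.69) | 0.15 (-0.25 to 0.55) |
| 0.5 | 45.7% | 489 | 0.40 (-0.58 to 1.38) | 0.11 (-0.39 to 0.62) |
| 0.75 | 62.4% | 338 | 0.60 (-0.87 to 2.07) | 0.08 (-0.45 to 0.62) |
| 1.0 | 71.5% | 257 | 0.80 (-1.16 to 2.76) | 0.06 (-0.48 to 0.61) |
| 1.5 | 80.8% | 173 | 1.20 (-1.74 to 4.14) | 0.04 (-0.51 to 0.60) |

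With no shift at all, the share excluded runs from 4.6% (SD 0.25) to 73.9% (SD 1.5). In the table, the all-pairs bias rises with the SD while the PP bias falls, so the PP set would show a smaller bias for a worse device.

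**The case against.** The best defence is that no sentence says pairs beyond 0.5 g/dL are removed. The only stated use of the flag is to record a failure percentage. The exclusion follows only if reference errors in one paragraph are equated with errors in the next, and the article then explains PP in terms of technician departures, with outliers and errors as their possible result. Other parts of the article treat large differences as signal: the sample size section values the chance of catching the most extreme differences, and Objective 3 models the absolute difference as an outcome. Both analyses are planned, and ITT keeps everything.

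Much of this stands. A reader might infer that the plan orders discordant pairs to be discarded; the text permits that reading but does not settle it. A reader might also infer that the study would present a poor device as agreeing within about half a g/dL. The documents do not support that, because the all-pairs limits are to be reported alongside and PP is nowhere named as primary. Nor do the PP limits take the same value whatever the SD: at SD 0.25 they are about -0.25 to 0.55.

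It does not dispose of the point. The definition that an analyst would apply says errors, and the preceding paragraph has just said that these pairs are errors. The narrower explanation shows that the section conflicts with itself; it does not resolve the conflict. Having a sound ITT analysis does not make an outcome-selected PP analysis valid. Nor is this detail left to an analysis plan: the article itself fixes both the error criterion and the exclusion.

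**Conclusion.** The point holds as a conflict in the text with a biasing literal reading. Under that reading the PP set is truncated on the SpHb-CBC difference, and its bias and limits of agreement cannot be interpreted as properties of the device. The damage is confined to the PP analysis.

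The size depends on an SD that the article does not give. With normal differences and the pilot shift, exclusion runs from about 12% of pairs at SD 0.25 to about 81% at SD 1.5 g/dL, and no PP limit exceeds about 0.62 g/dL in size anywhere in that range. The direction does not depend on the assumed SD.

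Only bias, SD and limits of agreement were calculated. It is tempting to extend the conclusion to the ICC, positive and negative percentage agreement and kappa, but the effect on those was not computed and no size is claimed for them.

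**What to change.** Amend the Corrective action text and the analysis-set definition as follows.

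1. Define PP exclusions only by process causes recorded without reference to the paired difference: incorrect device setting, the device's own signal-quality flags (stability, perfusion, SpHb confidence), and specimen problems such as hemolysis or a CBC analysed outside the time window in Table 1.
2. State that neither the 0.5 g/dL flag nor an outlier identified from the result is a ground for PP exclusion.
3. Report the percentage of pairs beyond 0.5 g/dL as an agreement result, separate from the percentage of process failures.
4. Base the agreement conclusion on the all-pairs analysis, with PP as a sensitivity analysis.

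The cost is wording only: the process causes are already to be documented, and sample size and visits are unchanged. The downside is that PP results will look less favourable than under the literal rule.

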## Statistical analysis plan

All analyses will be conducted in R and STATA.

### Objective 1: Deviations/agreement between SpHb and CBC

**
*Intraclass correlation coefficient*
**

The intraclass correlation coefficient (ICC) is a measure of similarity of within-group values in clustered data
^
12
^. Here the ICC (with 95% CI) will be used to evaluate the degree of agreement of hemoglobin values using the degree of variances between SpHb and CBC measurements with respect to variances within SpHb measurements and variances within CBC measurements. Observed ICC with 95% CI will be reported.

**
*Bland–Altman analysis*
**

Bland–Altman (B&A) analysis is a recommended analytical method of assessing the comparability between different techniques/methods using a graphical approach using mean differences and agreement intervals. It will be used to estimate agreement between the two instruments used to measure hemoglobin levels on a continuous scale
^
13,
14
^. The quantification of agreement between two measurements is assessed by determining the mean difference on two quantitative measurements (i.e., the mean difference between the two observers or techniques), their standard deviation and constructing limits of agreement.

Given that multiple repeated measurements are measured on the same participant at different gestational ages, the variances in the ICC and B&A analyses will be calculated according to the data structure. For repeated measures, using the differences between SpHb and CBC measures, both, between variance and within variance will be calculated as follows: 

$$\begin{array}{c} Var(\underline{\delta }\text{.})=\frac{Var_{between}}{n}+\frac{Var_{within}}{n*n_{r}},\\ Var_{between}=\frac{\sum_{i=1}^{n}\;{\left({\underline{\delta }}_{i.}-{\underline{\delta }}_{..}\right)}^{2}}{n-1}\\ {Var}_{\mathrm{within}}=\frac{\sum_{i=1}^{n}\;\sum_{j=1}^{n_{r}}\;{\left(\delta_{ij}-{\underline{\delta }}_{i.}\right)}^{2}}{n(n_{r}-1)} \end{array}$$

Where, subscript
*i* and
*j* denote participant (
*i*) and repeated blood sample (
*j*), where we have
*i*=1,...,
*n* participants and
*j*=1,...,
*n
_r_
* repeated blood samples per participant,
*δ
_ij_
* is the difference between the SpHb and CBC measurements from participant i blood sample j,

*δ
_i_
*
. is the average difference of all repeated samples from participant i,

*δ*
.. is the average difference from all participants and all repeated samples.

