## Methods

### Study design

This proposed study will use a prospective cohort design nested within the ongoing PRISMA MNH open cohort study (see
Figure 1). Three sites currently using Masimo devices will participate: Lusaka, Zambia; Kisumu and Siaya, Kenya; Karachi, Pakistan. Each site has identified defined geographic regions that are appropriate for longitudinal data collection and the conduct of ongoing research involving pregnant women. Hemoglobin measurements for the validation study will occur at five timepoints: <20 weeks, 20 weeks, 28 weeks, 36 weeks’ gestation, and six weeks postpartum. The study sites in Pakistan will also collect measurements at week 32.

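### The printed variance of the mean SpHb–CBC difference counts within-woman variance twice and holds only for equal visit numbers; the effect on the bias is conservative and small

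*Protocol article*

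**What the plan says.** The abstract names the ICC and Bland–Altman analysis as the methods for the primary objective. The section on Objective 1 describes Bland–Altman as finding the mean difference, "their standard deviation and constructing limits of agreement". Because each woman is measured repeatedly, it adds that "the variances in the ICC and B&A analyses will be calculated according to the data structure", and then: "For repeated measures, using the differences between SpHb and CBC measures, both, between variance and within variance will be calculated as follows".

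Three formulas follow, in the differences δ_ij between the SpHb and CBC readings of woman i at sample j:

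- Var(mean δ) = Var_between/n + Var_within/(n·n_r)
- Var_between = Σ(δ_i. − δ..)²/(n − 1), where δ_i. "is the average difference of all repeated samples from participant i"
- Var_within = ΣΣ(δ_ij − δ_i.)²/(n(n_r − 1))

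A single n_r stands for the number of "repeated blood samples per participant". No formula is printed for the variance of one difference or for the ICC. The ICC is described in words only, as agreement judged "using the degree of variances between SpHb and CBC measurements with respect to variances within SpHb measurements and variances within CBC measurements".

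Study design plans five time points and adds: "The study sites in Pakistan will also collect measurements at week 32". The sample size section speaks of three repeated measures. The Corrective action section defines a per-protocol analysis that leaves out outliers and errors. The Missing data section expects missing readings and compares multiple imputation with a complete-case analysis.

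**The concern.** The first formula is the familiar one for a mean of clustered data, but it is valid only when its first term contains the pure between-woman component. The printed Var_between is the raw variance of the participants' means, which already includes a share of the within-woman error. The confidence interval for the bias would therefore be wrong, and this is a primary analysis.

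Two further points follow from the same block of text. A single n_r does not fit the data that the protocol itself expects. The only combined variance shown is that of a mean, and it is introduced for both the limits of agreement and the ICC. The limits need the variance of a single difference, and the ICC needs the variances of the readings.

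**Working it through.** **Inputs.** From the document: the three formulas (Objective 1), n = 900 per site and a pilot shift of about 0.8 SD (Total sample size), and five visits, six in Pakistan (Study design) or three (Total sample size). Assumed: the between-woman share ρ of the variance of a single difference. The document gives no split, so a range is shown. The variance of a single difference is set to 1.

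**The plan's own figure.** The formula has no stated numerical result. The nearest figure is 90% power for a shift of 0.108 SD with 900 pairs. A two-sided one-sample t-test gives 89.9%, so it reproduces. It does not use the formula examined here.

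**Step 1: expectation.** Let δ_ij = μ + u_i + e_ij, with variances σ_b² = ρ and σ_w² = 1 − ρ. With n_r visits per woman:

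- E[Var_between] = σ_b² + σ_w²/n_r
- E[Var_within] = σ_w²
- True variance of the mean = (σ_b² + σ_w²/n_r)/n, which is E[Var_between]/n
- Expectation of the printed formula = (σ_b² + 2σ_w²/n_r)/n

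**Step 2: size at n_r = 5 and n = 900.** The half-width of the 95% interval is 1.96 × √(V/900), where V is n times the variance of the mean.

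| ρ | V true | V printed | SE ratio | Half-width true | Half-width printed |
|---|---|---|---|---|---|
| 0 | 0.20 | 0.40 | 1.414 | 0.029 | 0.041 |
| 0.25 | 0.40 | 0.55 | 1.173 | 0.041 | 0.048 |
| 0.50 | 0.60 | 0.70 | 1.080 | 0.051 | 0.055 |
| 0.75 | 0.80 | 0.85 | 1.031 | 0.058 | 0.060 |

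The excess is at most about 0.012 SD. At ρ = 0.5 the SE ratio is 1.118 for three visits and 1.069 for six. Simulation with 900 women agreed with the algebra at ρ = 0, 0.2, 0.5 and 0.8 for three, five and six visits.

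**Step 3: limits of agreement.** These need σ_b² + σ_w². With balanced data this is Var_between + (1 − 1/n_r)·Var_within, whose expectation is σ_b² + σ_w²/n_r + σ_w² − σ_w²/n_r = 1. Simulation returned an SD of 1.00 to within 0.001. The plain sum of the printed components has expectation 1 + σ_w²/n_r. At n_r = 5 its SD is √1.20 = 1.095 at ρ = 0 and √1.05 = 1.025 at ρ = 0.75, so limits built on it would be 2.5% to 9.5% too wide.

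**Step 4: unequal visits.** The divisor n(n_r − 1) is correct only if every woman has n_r pairs. As an illustration, suppose women average four of five visits and n_r = 5 is entered. The divisor is then 4n where 3n is needed, and Var_within is 25% too low. At an average of three of five it is 4n against 2n, and 50% too low.

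**Step 5: ICC.** Differences cancel the woman's true hemoglobin. Assume no bias and equal error variance of 0.5 per method, so the differences have variance 1. Then ICC = σ_T²/(σ_T² + 0.5). Assumed true-hemoglobin SDs of 0.5, 1.0, 1.5 and 2.0 give 0.33, 0.67, 0.82 and 0.89. The same components of the differences are therefore compatible with very different ICCs.

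**The case against.** The strongest reply is that the proven error is small and safe. It widens the interval for the bias, and the 41% figure needs a complete absence of between-woman variance. Against a pilot shift of about 0.8 SD, an extra 0.012 SD changes no conclusion. This stands, and it limits the weight of the point.

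A reader might infer that the limits of agreement will be built from the variance of the mean. At n = 900 and five visits its square root is √(0.40/900) = 0.021 to √(0.85/900) = 0.031, so the limits would be roughly 30 to 50 times too narrow. The text does not prescribe this. It labels the formula as the variance of the mean difference, a legitimate quantity for the interval around the bias, and mentions the SD and the limits separately. Nor does it say that the printed components are to be summed. An article may leave the explicit limits formula to the analysis plan.

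A reader might also infer that the ICC will be the between-woman share of the variance of the differences, which would measure the stability of a woman's device error rather than agreement. No such formula is printed, and the verbal description refers to the SpHb and CBC measurements. What remains is loose wording that ties the ICC to a block written only in differences.

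On visit numbers, site-specific analyses are planned, so Pakistan's extra visit upsets the balance only if sites are pooled, and imputation would restore balance in the imputed data. The complete-case comparison and the per-protocol set remain unbalanced.

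**Conclusion.** The printed variance of the mean difference is wrong as written. For balanced data it counts σ_w²/n_r twice, and at five visits it inflates the standard error of the bias by between 3% (75% between-woman share) and 41% (no between-woman variance). The algebra is exact; the size rests on an assumed variance split. The error is conservative, would not alter the conclusion at the pilot shift, and leaves the sample size figures untouched.

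The formula is also unsuited to unequal visit numbers, which the protocol's own handling of missing and erroneous readings will produce. For the limits of agreement and the ICC the finding is narrower: the text does not specify a wrong calculation, but the block it attaches to both does not supply the quantity that either needs.

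**What to change.** - **Standard error of the bias.** With equal visits, either drop the second term or keep both terms and replace Var_between by σ_b² = Var_between − Var_within/n_r.
- **Unequal visits.** Estimate σ_b², σ_w² and the standard error of the bias from a random-intercept mixed model on the differences.
- **Limits of agreement.** State that they are the mean difference ± 1.96·√(σ_b² + σ_w²), which with balanced data uses Var_between + (1 − 1/n_r)·Var_within. Say that neither the variance of the mean nor the plain sum of the printed components is used.
- **ICC.** State that it is an absolute-agreement ICC computed from the SpHb and CBC readings themselves, and detach it from the formulas in the differences.

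The cost is a few lines of text and standard R or Stata code. No new data are needed, the sample size does not change, and Objective 3 already uses linear mixed models.
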